**Patient self management**					
SMA-S	Interview patient		**X**	**X**	

*T0 = within 48 hours of hospital admission; T1 = 3 months after hospital admission; T2 = 12 months after hospital admission; * MDS = Minimal Data Set; SF-20 = Short Form 20; EQ6D = EuroQol; SPF-IL = Social Production Function questionnaire; SPPB = Short Physical Performance Battery; LAPAQ = LASA physical activity questionnaire; MMSE = Mini Mental State Examination; NPI = neuro-psychiatric index;; GeDS = Geriatric Depression Scale; GloDS = Global Deterioration Scale;; SMA-S = Self Management Ability Scale.

**Table 3 T3:** Effect evaluation: Data collection of informal caregiver outcome variables

Informal caregiver outcome variables + instruments	Data collection methods	Data collection times			Notes
		**T0**	**T1**	**T2**	

**Quality of life**					
EQ-6D	Mailed paper questionnaire	**X**	**X**	**X**	Part of MDS
SF20	Mailed paper questionnaire	**X**	**X**	**X**	5 items part of MDS
Carer QoL	Mailed paper questionnaire	**X**	**X**	**X**	Part of MDS
**Burden of care**					
ARS (objective)	Mailed paper questionnaire	**X**	**X**	**X**	Part of MDS
Questions on time spent on care tasks	Mailed paper questionnaire	**X**	**X**	**X**	
CSI (subjective)	Mailed paper questionnaire	**X**	**X**	**X**	
SRBS (subjective)	Mailed paper questionnaire	**X**	**X**	**X**	Part of MDS

*T0 = within 48 hours of hospital admission; T1 = 3 months after hospital admission; T2 = 12 months after hospital admission; * MDS = Minimal Data Set; SF-20 = Short Form 20; EQ6D = EuroQol; GeDS = Geriatric Depression Scale;; ARS = Activity restriction scale; CSI = Caregiver strain index; SRBS = Self-rated burden scale.

**Table 4 T4:** Process evaluation: Data collection of process outcome variables

Outcome variables and instruments	Data collection methods	Data collection times			Notes
		**T0**	**T1**	**T2**	

**Patient experiences with quality of care**					
PACIC	Interview patient		**X**	**X**	
(H)CAPHS	Interview patient		**X**		
**Caregiver experiences with quality of care**					
SASC - adapted for elderly care (+ own formulation additional questions)	Mailed paper questionnaire			**X**	
**Process of care delivery hospital**					
Process indicators (own formulation)	Medical registers	**X**			+ time after hospital discharge
**Process of care delivery professional view**					
TCI (+ own formulation additional questions)	Mailed paper questionnaire				Last months inclusion period
ACIC (only partly)	Mailed paper questionnaire				Last months inclusion period
RCSP	Mailed paper questionnaire				Last months inclusion period

* T0 = within 48 hours of hospital admission; T1 = 3 months after hospital admission; T2 = 12 months after hospital admission * PACIC = Patient Assessment of Chronic Illness Care; (H)CAPHS = (Hospital) Consumer Assessment of Healthcare Providers and Systems; SASC = Satisfaction with Stroke Care Questionnaire; TCI = Team Climate Inventory; ACIC = Assessment of Chronic Illness Care; RCSP = Relational Coordination Survey for Professionals.

**Table 5 T5:** Cost effectiveness evaluation: Data collection health care volumes and prices

Outcome variables	Data collection methods	Data collection times			Notes
		**T0**	**T1**	**T2**	

**Health care volumes**					
Period hospital admission:	Hospital registries	Time of hospital discharge			+ during inclusion
*- amount of hospital days (days admitted)*	Hospital registries	Time of hospital discharge			
*- total days/time admitted at ICU*	Hospital registries	Time of hospital discharge			
*- amount of consults medical/paramedical*	Hospital registries	Time of hospital discharge			
*- amount of large scans and diagnostics*	Hospital registries	Time of hospital discharge			
*- amount of large treatments/operations*	Hospital registries	Time of hospital discharge			
*- wrong bed days*	Hospital registries	Time of hospital discharge			
*- amount of days admitted*	Hospital registries	Time of hospital discharge			
*- amount of consults medical/paramedical*	Hospital registries, interviews personnel	Time of hospital discharge			+ during inclusion
*- time/amount of multidisciplinary meetings*	Hospital registries, interviews personnel	Time of hospital discharge			+ during inclusion
Health care utilization patient in periods before and after hospital stay	Interview patient and mailed paper questionnaire primary caregiver	**X**	**X**	**X**	
*- homecare/nursing home/etc*					
Average time per consult	Interviews professionals (sample)	During inclusion period			
Amount informal care	MDS + questionnaire informal caregiver	**X**	**X**	**X**	Amount in hours
Amount (multidisciplinary) coordination	Interviews professionals				Amount in hours
**Health care prices**					
price per hospital day	DBC information + manual cost research	Retrospective			Similar calculations for prices hospital, CPH, care hotels etc.
price per day/hour admitted at ICU	DBC information + manual cost research				
price of consults medical/paramedical	DBC information + manual cost research				
price of large scans and diagnostics	DBC information + manual cost research				
price of large treatments/operations	DBC information + manual cost research				
costs of home care/other care	Integral costs per product cluster	Retrospective			
costs informal care by primary caregiver	Market price/missed wages & time	Retrospective			
travel costs (average)	Literature	Retrospective			

*T0 = within 48 hours of hospital admission; T1 = 3 months after hospital admission; T2 = 12 months after hospital admission.

#### Demographics and triage (table 1)

##### Triage: identification of elderly at risk for functional loss

Triage data is gathered within 48 hours of hospital admission in order to identify elderly at risk for functional loss at an early stage. Based on the pilot results the Identification of Seniors At Risk-hospitalized patients (ISAR-HP) is chosen as the main triage instrument in order to achieve information on a combination of factors that have shown to be important in predicting functional loss. The ISAR HP questionnaire is administered to the patient and consists of four questions on education and need of help with travelling, walking or help with housekeeping in the period before admission to the hospital [46]. A person is considered at risk for functional loss and is therefore eligible for treatment with the program if he/she scores one or higher on the ISAR HP. This is a different score from the originally set cut off score of 2 or higher as is stated in the paper written by Buurman et al (2010), and can be explained by the differences in characteristics and diagnoses of the studied population. In addition, the NPI-Q and MMSE are administered in order to identify elderly who are eligible for an additional stay at the centre for prevention and reactivation as part of the program. Patients will be considered eligible for a stay at the reactivation centre when they score 2 or higher on the ISAR HP and/or 3 or higher on the NPI-Q and/or 27 or lower on the MMSE. The Neuropsychiatric index (NPI-Q) is the validated short version of the NPI [49]. It aims to identify neuropsychiatric symptoms present in the patient in the last month by means of twelve symptoms (e.g. delusions, aggression, hallucinations) and also measures the emotional burden for the caregiver. The NPI is administered to the primary informal caregiver of the patient by means of a telephone interview at time of hospital admission. The Mini Mental State Examination (MMSE) measures cognitive functioning by means of interviewing the patient using questions on orientation in time and space, short-term and middle-term memory, comprehension and other cognitive dimensions [50,52].

##### Demographics

Data on demographics (e.g. age, socioeconomic status, marital status, and gender) is gathered at T0, T1 and T2 by means of the Minimal Data Set (MDS) and hospital registries. The MDS is developed in light of the national program elderly care in the Netherlands and aims to compare elderly persons as well as their caregivers participating in different projects in the Netherlands by measuring demographics, quality of life, ADL functioning, experienced health and health care utilization (patient-level) as well as demographics, experienced health and burden of care, quality of life, and objective burden of care (informal caregiver level). The MDS is a combination of (parts of) validated questionnaires and is administered by trained research nurses and trained students (e.g. medical students or other students who have experience with research and/or elderly care), who interview patients at T0, T1 and T2. The data is collected from informal caregivers by means of mailed paper questionnaires, which are self-administered by informal caregivers and then sent back to researchers. A reminder including an extra copy of the questionnaire is sent to informal caregivers if they did not send back the first questionnaire. Additional data on demographics as well as data for other elements of the evaluation (e.g. medication, diagnosis, specialist consults) is collected from medical registries after hospital discharge.

#### Effect evaluation (tables 2 and 3)

All outcome data of the patient are collected by the same means as the MDS described above.

##### Quality of life (patient)

The EuroQol (EQ6D) is administered to measure quality of life among patients and their caregivers. It is part of the MDS and will be used to calculate cost-utilities of health care [53].

The Dutch version of the SF-20 is administered and aims to score 6 sub-dimensions such as physical functioning, social functioning and experienced health [54]. The SF-20 is chosen since it is quick to administer and many of its questions are already part of the MDS. The SF-20 has shown good test-retest reliability and acceptable convergent and discriminative validity for a group of elderly persons, even though some precaution is advised in using the questionnaire with elderly people living at home [55]. The short version of the Social Production Function Scale SPF-IL scale measures social well-being by means of the dimensions "affection", "behaviour confirmation" and "status" as well as physical well-being by means of the dimensions "comfort" and "stimulation" [56].

##### Physical functioning (patient)

The Katz-15 index of activities of daily living measures function over time by means of questions on several domains such as bathing, dressing, toileting, transferring, continence and feeding [57,58]. The LAPAQ (LASA Physical Activity Questionnaire) is an interview administered questionnaire measuring frequency and duration of activities such as household activities, walking, gardening and sports [59]. The SSPB (short physical performance battery) is an objective physical performance test consisting of repeated chair stands (number of stands and amount of time standing), balance testing (three different stands), and walking (2.44 meters). This test is necessary in order to see if the results from the subjective physical performance tests are in agreement with measured objective physical capabilities [60,61].

##### Cognitive and neuropsychiatric functioning (patient)

The NPI and MMSE (see triage for explanation) are administered to measure cognitive and neuro-psychiatric functioning over time, with the short version of the MMSE being administered at follow up instead of the longer version that was administered at time of hospital admission. Nevertheless, the results are still comparable using existing and tested transformation scores. The Global Deterioration Scale (GDS) measures a patient's stage of dementia by means of 7 levels, from 1 (normal functioning) to 7 (very serious dementia) and is administered to the informal caregiver of the patient [62].

##### Social and psychological functioning (patient)

The Geriatric Depression Scale (GDS-15) identifies and measures functional as well as mood symptoms of depression [63]. The GDS-15 has been validated in geriatric inpatients as well as in primary care and community-living elderly [64,65]. The Loneliness scale consists of 11 questions and measures social functioning of the patient [66].

##### Self-management (patient)

The SMA-S (Self Management Ability Scale) measures the ability of a person to manage his/her own general daily life activities in the past months. It contains items on several subjects such as activities the patient initiates; activities the patient starts now but expects to benefit from later; general activities; combining activities; the success or failure of activities; and dealing with adverse experiences [67].

##### Quality of life (caregiver)

The carer quality of life questionnaire (Carer QoL) measures quality of life of caregivers and is part of the MDS [68]. The EuroQol is also administered to the caregiver as part of the MDS (see Quality of Life patients).

##### Burden of care (caregiver)

Objective burden of care for the caregiver is measured using the Activity Restriction Scale [69] and additional questions on objective burden of care [70,71]. Subjective burden of care is measured with the Self Rated Burden Scale and Caregiver Strain Index or CSI [72,73].

#### Process evaluation (table 4)

The process evaluation will look at process indicators thereby showing the extent to which the new program leads to better structure and process of care in comparison with other usual forms of geriatric care in two other hospitals in the same region (e.g. improvements in coordination between care-providers, patient logistics, information logistics and support). In addition, the process evaluation will focus on how and to what extent the program is actually implemented according to plan. This requires measuring instruments that are sensitive for specific interventions and which are connected with the expected alternations in the outcomes of care for the elderly and caregiver. In order to do this, sub-domains of the care process from a patient, caregiver and professional point of view will be measured. In addition, qualitative data is gathered to explain quantitative outcomes. Described processes and provided interventions will be linked to outcomes in order to provide a complete description of the evaluation of this transition project.

##### Process of care (patients)

Patient experiences with delivered care are measured at T1 by means of the Patient Assessment of Chronic Illness Care (PACIC) questionnaire, and consists of questions on care received in the last 3 months [74]. In addition, specific experiences with hospital care delivered during total hospital stay around T0 are measured with the (Hospital) Consumer Assessment of Healthcare Providers and Systems ((H)CAHPS), which consists of questions on treatment by nurses and doctors, hospital environment, experiences with hospital stay as well as discharge from the hospital, and general appreciation for the hospital [75]. Registering process indicators involves a continuous measurement of the care provided to the elderly and their caregiver. At this time it does not appear possible to make use of an Electronic Patient Dossier (EPD) in all three hospitals. Therefore, process indicators will be collected partly from existing registrations. The remaining indicators are collected by research nurses and students. Insight into the care process is provided by covering the topics of 'determining vulnerability'; 'provided medical care (diagnostics and treatments)' and 'the extent of multidisciplinary meetings'.

##### Experiences quality of care (caregiver)

The SASC (Satisfaction with Stroke Care Questionnaire) originally measures patient satisfaction with stroke care. For current research, it has been adapted to caregiver satisfaction with the care for vulnerable elderly after discharge. It covers subjects on both the acute and chronic phase of care: experienced caregiver respect and information provision during elderly hospital stay; the amount of caregiver support and information provision after elderly discharge [76,77]..

##### Process of care (professional)

The TCI (Team Climate Inventory) has been used as an improvement tool for assessing team function to identify areas that could be improved. It contains 14 items on several team dimensions such as: task orientation and support for innovation [78]. The ACIC (Assessment of Chronic Illness Care) is a practical quality-improvement tool to evaluate the delivery of care for chronic illness in six areas: community linkages; self-management support; decision support; delivery system design; information systems and organisation of care [79]. The RCSP (Relational Coordination Survey for Professionals) measures the relational dynamics of coordinating work. The self-administered questionnaire contains 8 items. Different professionals are asked how frequently, timely and accurately they solve problems and share goals with other professionals while treating vulnerable elderly [80].

##### Qualitative process measures

Qualitative measures will complement the quantitative data collection, thereby strengthening the study design by providing the mixed method component mentioned earlier. Qualitative measures will provide additional in-depth information on the context in which the implementation of care and interventions takes place (structure). An audit study based on expert opinion and literature will provide information on general quality of care (e.g. by means of showing/evaluating differences and similarities in the care and interventions that are provided in the three hospitals). Furthermore, a fidelity study will collect information on the differences between planned and actual implementation of care and interventions in the hospitals (is care implemented as it should be by the professionals?). Finally, case studies by means of qualitative interviews with professionals as well as observations within the hospitals will provide further information and insight as they provide a context in which quantitative outcomes can be placed.

#### Cost-effectiveness evaluation (table 5)

A cost-utility analysis will compare cost differences (incremental costs) of provided health care in the three hospitals with the difference in health effects measured in quality adjusted life years (QALYs). QALYs combine alterations in quantity and quality of life (mortality and morbidity) into a combined generic instrument. Data on quality of life will be measured by means of the EQ6D and SF20 for patients and by means of the EQ6D, CarerQoL and SF-20 for the primary informal caregiver (see effect evaluation). Cost information is gathered by means of hospital information systems, patient files and questionnaires for both patient and primary caregiver at baseline (T0), after three months (T1) and after 12 months (T2). A societal perspective is used; taking into account both direct and indirect costs within as well as outside health care. Data collection on utilization of care in hospital (nursing days, diagnostic and therapeutic activities and out-patient visits), nursing home (days), rehabilitation (admissions/outpatient), and home care (care hours according to product clusters) will take place centrally, according to a standard method, by means of standardized files and standard cost diaries as well as through patient and caregiver questionnaires

### Data analysis

#### Triage

Data will be gathered on risk factors for functional decline and predictive models for functional decline at 3 and 12 months can be developed using multivariate regression techniques and data from control settings. The quality of the predictive models will be assessed by explained variance for continuous outcome measures and by ROC-curves for dichotomous outcome measures. The quality of the model that fits the program eligibility criteria will be compared to models with other risk factors involved and/or other cut-off points on the triage instruments. This way the added value of another triage method can be objectively assessed. These analyses were already partly done using preliminary pilot study results but will be repeated using final results of the main evaluation study. Furthermore, main study results will be used to evaluate the validity of the model(s) with internal validation techniques (bootstrapping) and cross validation between the three settings whereby each setting acts as a test-population for model(s) developed in the other settings [81].

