### Objectives of the evaluation

This evaluation study entails an effect, process and cost evaluation of offered geriatric health care and has four main objectives. First of all, the study aims to determine to what extent the program, in comparison with other usual forms of geriatric care, leads to a retention in functioning and quality of life of at risk elderly, a reduction in the burden of care for the patient's primary informal caregiver, shorter lengths of hospital stay, and a reduction of 'wrong bed' problems as well as (re-) admission to hospitals, nursing homes and mortality. In addition, it will show the extent to which program care including a stay at a reactivation centre, leads to better functioning and quality of life of elderly patients in need of complex care. Secondly, the study aims to determine to what extent the triage instruments used in the program detect increased risk for functional loss and to determine how criteria for triage should be adjusted to optimally link the offered interventions to the needs of the individual elderly at risk. Thirdly, the evaluation will determine to what extent the program, in comparison with other, usual forms of geriatric care in the Netherlands, leads to a better structure and process of care. Finally, the cost-effectiveness of the program (both including and excluding a stay at a reactivation centre) will be determined in comparison with other usual forms of geriatric hospital care in the Netherlands.

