#### Inclusion criteria

• patients aged 65 years or older

• admitted in one of the participating hospitals and staying >48 hours

• at risk for functional loss (ISAR HP ≥ 1)

Additional criteria for a stay at the centre for prevention and recovery

• ISAR HP ≥ 2 and/or MMSE ≤ 27 and/or NPI ≥ 3

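### Triage cut-offs are compared on ROC curves and explained variance in a cohort that contains only patients with ISAR-HP ≥ 1, so the comparison favours any informative stricter ISAR-HP cut-off and gives no weight to missed decliners

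*Protocol article*

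**What the plan says.** The second objective (Objectives of the evaluation) is partly to "determine how criteria for triage should be adjusted to optimally link the offered interventions to the needs of the individual elderly at risk".

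The analysis that serves it is under Data analysis, Triage. The performance measures are fixed there: "The quality of the predictive models will be assessed by explained variance for continuous outcome measures and by ROC-curves for dichotomous outcome measures". The model that matches the programme's eligibility criteria "will be compared to models with other risk factors involved and/or other cut-off points on the triage instruments". The section concludes: "This way the added value of another triage method can be objectively assessed". It says that part of this work was done on preliminary pilot results and will be repeated on the final main-study results. It also plans "internal validation techniques (bootstrapping) and cross validation between the three settings whereby each setting acts as a test-population".

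Entry to the main study is restricted on the main triage instrument. The third inclusion criterion begins "at risk for functional loss (ISAR HP ≥ 1", and the Population section says that patients identified by the ISAR-HP are the ones asked to take part. The pilot (Pilot study) had no such restriction. It approached all patients aged 65 or over in the intervention hospital, with around 500 included at baseline and around 300 followed up at three months.

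**The concern.** The section moves from two general performance measures to a claim that one triage method can be shown objectively better than another. A choice between cut-offs weighs decliners who are missed against patients flagged needlessly, and the section states no such weight. ROC area supplies one by default, because a point of sensitivity counts the same as a point of specificity whatever the frequency of decline or the programme's capacity.

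The enrolment rule makes this worse. The comparison is to be repeated in data where everyone already satisfies the current entry rule, so that rule cannot separate patients at all. The planned measures would then make it look worthless next to almost any stricter ISAR-HP cut-off. At stake is the advice on how the triage criteria should change.

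A secondary point concerns fitted regression models for dichotomous outcomes. ROC area does not show whether predicted risks are right in another hospital.

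**Working it through.** The article gives no ROC area, sensitivity, specificity or explained variance for triage, so there is no stated figure to reproduce.

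**Step 1. The current entry rule in the main cohort (no assumed accuracies).** Everyone enrolled has ISAR-HP ≥ 1, so the rule flags everyone: sensitivity (Se) = 1 and specificity (Sp) = 0.
- ROC area of a cut rule = (Se + Sp)/2 = (1 + 0)/2 = 0.50.
- A predictor with one value explains none of the variance of any outcome, so explained variance = 0.
- A stricter ISAR-HP cut-off with Se + Sp > 1 has area above 0.50 and explained variance above 0. It misses at least as many decliners, because the current rule misses none in these data.

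**Step 2. Size, with assumed accuracies.** The 35% decline rate is the Background figure for 70-year-olds at discharge. The accuracies are assumptions: ISAR-HP ≥ 1 has Se 0.90 and Sp 0.40; ISAR-HP ≥ 2 has Se 0.70 and Sp 0.68 (case A) or 0.55 (case B). Formulas per 1,000 unrestricted patients: missed = 350 × (1 − Se); flagged = 350 × Se + 650 × (1 − Sp). Explained variance is the squared phi coefficient, the counterpart for a dichotomous outcome.

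| Rule | ROC area | Explained variance | Missed | Flagged |
|---|---|---|---|---|
| ≥ 1 | 0.650 | 0.098 | 35 | 705 |
| ≥ 2, case A | 0.690 | 0.133 | 105 | 453 |
| ≥ 2, case B | 0.625 | 0.057 | 105 | 538 |

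In case A both measures prefer the rule that misses three times as many decliners. In case B both prefer ≥ 1. With case A accuracies, missed decliners are 20 against 60 at 20% decline (assumed), and 65 against 195 at 65% (the Background figure for age 90 or over).

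**Step 3. The same patients after restriction to ISAR-HP ≥ 1.** The 705 flagged by ≥ 1 comprise 350 × 0.90 = 315 decliners and 650 × 0.60 = 390 others. Of the 315, the ≥ 2 rule keeps 350 × 0.70 = 245, so its Se within the cohort is 245/315 = 0.778.
- Case A: false positives 650 × 0.32 = 208; Sp = (390 − 208)/390 = 0.467; area = 0.622; explained variance 0.064.
- Case B: false positives 650 × 0.45 = 292.5; Sp = (390 − 292.5)/390 = 0.250; area = 0.514; explained variance 0.001.
- The ≥ 1 rule: area 0.500; explained variance 0.

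In case B, restriction alone reverses the ranking, from 0.650 against 0.625 in favour of ≥ 1 to 0.500 against 0.514 in favour of ≥ 2. The 35 decliners whom ≥ 1 misses are absent from the restricted data.

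**Step 4. What a stated weight does.** Net benefit at risk threshold t = 0.35 × Se − 0.65 × (1 − Sp) × t/(1 − t), in the unrestricted sample. Flagging everyone sets Se = 1 and Sp = 0.

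| t | Flag everyone | ≥ 1 | ≥ 2, case A | ≥ 2, case B |
|---|---|---|---|---|
| 10% | 0.278 | 0.272 | 0.222 | 0.213 |
| 20% | 0.188 | 0.218 | 0.193 | 0.172 |
| 30% | 0.071 | 0.148 | 0.156 | 0.120 |

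In case A the preferred rule changes with t, from flagging everyone to ≥ 1 to ≥ 2. The threshold settles the choice, and the section states none. In case B, ≥ 2 is below ≥ 1 at all three thresholds, although the restricted ROC area prefers it.

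**Step 5. Calibration.** In a simulation (20,000 patients, score 0 to 5, log-odds of decline −2 + 0.6 × score), predicted risks were cubed. Their mean fell from 0.40 to 0.12 against an observed 0.41. ROC area stayed at 0.761; explained variance went from 0.204 to −0.170.

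**The case against.** The strongest reply is that the text says ROC curves and never says that the largest area wins. A curve shows sensitivity and specificity at every cut-off, and that is much of what a reader needs. This stands in part: no selection rule is written, so the default to area is an inference. But neither a curve nor an area supplies the weight between the two errors, and a curve drawn in the restricted cohort cannot show the patients below its entry point.

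It can also be said that the eligibility model might use the undivided ISAR-HP score or the additional criteria for a centre stay, which do vary within the cohort. That is so, and Step 1 applies only to the entry cut-off as a rule. The accuracies in Steps 2 to 4 are assumed, the 35% is loss at discharge and not at 3 or 12 months, and case B shows that no reversal need occur in unrestricted data. All of that stands; Step 1 needs none of these inputs.

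Four stronger readings are tempting and not supported.
- A reader might infer that these measures cannot rank cut-offs. They can: each dichotomised rule has its own area and explained variance.
- A reader might infer that poor calibration would distort the choice between ISAR-HP cut-offs. A rule on the raw score flags the same patients whatever the calibration. Explained variance of fixed predictions does react to miscalibration, so the gap concerns ROC area and fitted models.
- A reader might infer that validation is lacking. Bootstrapping and testing between hospitals are both planned.
- A reader might infer that the plan has already moved towards missing more patients. The one documented change of entry cut-off, from 2 to 1 (Demographics and triage), goes the other way.

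**Conclusion.** The point holds in a limited form. The named measures can rank triage rules, but they do not make the choice of cut-off objective, because they carry no stated weight for missed decliners. In the main-study data they are tilted by construction. The current entry rule is fixed at ROC area 0.50 and explained variance 0, any informative stricter ISAR-HP cut-off scores higher, and decliners below ISAR-HP 1 cannot be counted. This rests only on the inclusion criterion and on the statement that the analysis will be repeated on main-study results. The size (35 against 105 missed per 1,000, and the case B reversal) is illustrative and rests on the assumed accuracies and the 35% rate.

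The missing calibration check is a lesser matter, relevant to fitted models for dichotomous outcomes carried to another hospital. The consequence is confined to the triage objective; the hospital comparison and the nested randomised trial are untouched.

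**What to change.** Amend the Triage analysis text as follows.

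1. For the current rule, each alternative cut-off and each new model, report sensitivity, specificity, and numbers flagged and missed per 1,000. Add net benefit, with a flag-everyone comparator, at a risk threshold or programme capacity stated before the data are analysed.
2. Assess the ISAR-HP ≥ 1 entry cut-off only in the unrestricted pilot data, and state that main-study triage results apply within ISAR-HP ≥ 1.
3. For fitted regression models, add calibration intercept and slope in each test hospital to the validation already planned.
4. Keep ROC area and explained variance as descriptive measures, and drop the claim that they alone settle added value objectively.

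No new data are needed; the cost is some wording and a little extra analysis. There are two real drawbacks. The team must commit to one threshold or capacity in advance, and evidence on the entry cut-off will rest on one hospital's pilot, with around 300 patients followed up at three months.
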